## Methods/Design

The study is an 18 month multi-site cluster randomised controlled trial conducted in 8 sites in 7 PCTs in England, and managed by a central DESMOND Research Office. Ethical approval was received from Cambridgeshire Research Ethics Committee (07/H0304/129) and local research governance approval from participating PCTs.

Practices are randomised to one of two arms: 1) Participants attend a DESMOND structured education programme which includes a module on self-monitoring of blood glucose; and 2) Participants attend a DESMOND structured education programme which includes a module on self-monitoring of urine glucose.

### Setting and recruitment of PCTs

The study is being conducted in primary care in a cross-section of settings ranging from inner city to rural PCTs. Two criteria were used when approaching PCTs about participating in the study. First, they were required to have a team of accredited DESMOND educators who were interested and willing to participate. Second, PCTs needed to be willing to support the prescription requirements of the study. PCTs vary in their policy on the prescription of blood glucose monitoring strips for people with non-insulin treated T2DM, which can be a contentious issue due to the prescribing costs involved. Practices are refunded the cost of prescriptions for test strips to prevent the cost being a barrier to self-monitoring within the trial.

### Randomisation of practices

The study is cluster-randomised, with all enrolled participants in one practice randomised to one arm of the trial in order to avoid potential 'contamination' from participants randomised to different arms. Randomisation was carried out independently at the University of Leicester, after stratification for practice setting and list size. Two randomisation plans were computed, one for small and one for large lists sizes. ^a^Practices agreed to participate in the study before being randomised. Practices were not informed of their randomisation when recruited, but become aware of it during the study as participants attend the practice for clinical support and repeat prescriptions for monitoring resources.

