### Analysis

#### Power calculations and sample size

The aim is to show equivalence in mean HbA1c at 18 months of within ± 0.5%. Assuming a standard deviation (SD) at 18 months of 1.5%, [37] the sample size required without allowing for clustering for 80% power at 5% significance is 142 per arm. With an intra-cluster correlation of 0.05, [38] and an expected mean cluster size of 5, adjustment for clustering brings the number required to 170 per arm. Assuming 20% drop out and 20% non-consent, the numbers required are 266 referrals and 213 consents per arm.

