#### Statistical analysis

There will be double entry of all data and discrepant values will be investigated. Results will be reported according to CONSORT guidelines for cluster randomised trials and statistical analysis carried out on an intention-to-treat basis. Missing outcomes will not be replaced and an average over-time of continuous outcomes will be derived. This procedure will measure the cumulative effect of the treatment and have the maximum number of participants. Continuous variables will be analysed using a linear model adjusting for clustering using generalised estimating equations, and adjusting for baseline values.

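### How practice setting entered the randomisation is unclear, and the stated model leaves out the list-size stratum; the likely cost is a slightly over-wide interval

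*Protocol article*

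**What the plan says.** Under Randomisation of practices, the protocol article states that practices were randomised "after stratification for practice setting and list size". The next sentence reads: "Two randomisation plans were computed, one for small and one for large lists sizes". It does not define the categories of setting or say how setting entered either plan.

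Under Statistical analysis, the model is given in one sentence: "Continuous variables will be analysed using a linear model adjusting for clustering using generalised estimating equations, and adjusting for baseline values". Neither list size nor setting is named.

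Under Power calculations and sample size, the target is equivalence in mean HbA1c at 18 months within ±0.5%. The assumptions are an SD of 1.5%, an intra-cluster correlation of 0.05 and a mean cluster size of 5, giving 142 per arm before clustering and 170 after. Neither stratification factor enters this calculation.

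**The concern.** There are two linked points.

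First, the two sentences on randomisation do not fit together. Stratifying on two factors needs a plan for each combination, or some other device such as ordering practices by setting within a plan. Only a split by list size is described. Setting may have been dropped, or handled in a way not reported, and the reader cannot tell which.

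Second, list size restricted the randomisation whichever reading is right, but it is absent from the stated model. When allocation is balanced within strata that predict the outcome, differences between strata cannot contribute to the difference between arms. An analysis that ignores the strata still counts those differences as random error, so its standard error is too large. This trial succeeds only if the interval lies inside ±0.5%, so extra width makes equivalence harder to show.

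**Working it through.** **The plan's own figures.** The formula for a two-sided test of a difference gives n = 2 × [1.5 × (1.960 + 0.842) / 0.5]² = 141.3, so 142 per arm. The design effect is 1 + (5 − 1) × 0.05 = 1.2, and 142 × 1.2 = 170.4, in line with the stated 170. These figures reproduce and do not involve the strata, so nothing here changes them.

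**Inputs for the size of the effect.**
- From the sample-size section: SD 1.5 (variance 2.25) and ICC 0.05. Between-practice variance is 0.05 × 2.25 = 0.1125; within-practice variance is 0.95 × 2.25 = 2.1375.
- Participants analysed per practice: 2 × 170 = 340 over the 75 practices given under Involvement of practice nurses, so 340 / 75 = 4.53. The plan's own mean cluster size of 5 is used as a check.
- Assumed, because the documents give no figure: a difference d between small-list and large-list practices of 0.2, 0.3 or 0.4% HbA1c; about equal numbers of small-list and large-list practices; and allocation balanced within each plan.

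**Formula.** The variance of a practice mean is V = 0.1125 + 2.1375 / m. A balanced two-level factor contributes d² / 4 to it. The unadjusted standard error is too large by √[V / (V − d²/4)] − 1. For m = 4.53, V = 0.1125 + 0.4715 = 0.584. For m = 5, V = 0.1125 + 0.4275 = 0.540.

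| d (% HbA1c) | d²/4 | Share of between-practice variance | Excess SE, m = 4.53 | Excess SE, m = 5 |
|---|---|---|---|---|
| 0 | 0 | 0% | 0% | 0% |
| 0.2 | 0.0100 | 8.9% | 0.9% | 0.9% |
| 0.3 | 0.0225 | 20.0% | 2.0% | 2.2% |
| 0.4 | 0.0400 | 35.6% | 3.6% | 3.9% |

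**What that means for the interval.** At 170 per arm the unadjusted SE is 1.5 × √(2 × 1.2 / 170) = 0.178, so the 95% half-width is 1.96 × 0.178 = 0.349. Dividing by the m = 5 ratios 1.009, 1.022 and 1.039 gives 0.346, 0.342 and 0.336. On the plan's own difference formula, Φ(0.5 / SE − 1.96), power goes from 80.1% to 80.8%, 81.7% and 83.0%. That formula is not an equivalence power calculation; it is used here only to put the change on the plan's own scale.

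**Direction.** With an SE too large by those m = 5 ratios, a nominal 95% interval covers about 95.2%, 95.5% and 95.8%. A simulation of practice-mean regression agrees. It used 72 practices of 5, two list-size plans, and list size explaining a quarter of between-practice variance, with setting explaining another quarter. Leaving list size out gave a mean interval width of 0.689, against 0.672 with it in. Coverage was 95.8% against 95.2%. False claims of equivalence at a true difference of 0.5 were 2.2% against 2.8%, around a nominal 2.5% with Monte Carlo error of about 0.25 points. When neither factor predicted the outcome, adjustment gave no gain.

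**The case against.** The strongest reply is that this is a condensed article with one sentence on the model. Stratification covariates are often named in an analysis plan, which is not shown here, and the sentence does not say its list is complete. That is fair, and the missing term may already have been supplied elsewhere. What stands is that the article does list its adjustments and omits a factor that it says restricted the randomisation.

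The effect is also conditional. It needs list size to predict HbA1c after baseline HbA1c is in the model, and the documents are silent on that. The calculation uses the raw SD and ignores baseline adjustment, which could shrink the list-size difference, the residual variance or both. It also assumes balanced allocation within each plan. If each plan were simple randomisation, the unadjusted interval would be correctly calibrated, and adjustment would only sharpen it. All of this stands and limits the point to a modest one.

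A reader might infer that leaving out setting also makes the analysis mismatch the design. That follows only if setting was a stratum. If the two list-size plans were all that was used, setting was not a design factor and its omission creates no mismatch.

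A reader might also infer that chance imbalance between inner-city and rural practices would bias the result. It would not. Chance imbalance on an unstratified factor is sampling variation, which the unadjusted interval already allows for.

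**Conclusion.** The point holds in a limited form. The account of the randomisation needs reconciling, and at least the list-size stratum should be in the model. If list size predicts HbA1c after baseline adjustment, the unadjusted interval is roughly 1 to 4% too wide for assumed list-size differences of 0.2 to 0.4% HbA1c. At the upper end that is a half-width of 0.349 instead of about 0.336, and just under 3 power points on the plan's formula. If there is no association the loss is zero. The same reasoning applies to setting only if it was a stratum.

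Stronger readings are not supported. The documents do not show that precision is in fact lost. The interval errs on the safe side, so this omission gives no reason to fear a false claim of equivalence. The stated 142 and 170 per arm are not affected.

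**What to change.** Under Randomisation of practices, state the strata actually used. If setting was one, give its categories and say how it entered the two plans. If it was not, remove it from the description of the stratification.

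Under Statistical analysis, or in the analysis plan, add the strata actually used as fixed covariates in the primary and secondary models for continuous outcomes. List size belongs there in any case. Setting belongs there if it was a stratum; otherwise it is an optional covariate, to be included only if specified before the outcome data are analysed.

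The cost is a sentence or so in each place. List size takes one degree of freedom out of 75 practices. Setting, if included, takes the number of its levels minus one, which the article does not allow us to count. Both are practice-level characteristics used or named at randomisation, so no new participant data should be needed, and no change to the sample size follows.

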### Patient eligibility criteria

People with newly diagnosed T2DM were referred by their practice within 12 weeks of diagnosis. They were excluded if they were under 18 years, were taking insulin, had severe and enduring mental health problems, were not primarily responsible for their own care, were unable or unwilling to participate in a group programme (for example, housebound or unable to communicate in English), or were participating in another research study. They were not eligible if they had already started SMBG, (unless this involved informal 'trial and error' without instruction from a HCP and they were willing to be randomised to either type of monitoring). Participants were required to attend a DESMOND programme within 6 months of diagnosis.

### Referral and recruitment of participants

Practice nurses referred people who were newly diagnosed with T2DM and interested in participating in the study to the local DESMOND team. A member of the local DESMOND team then contacted each individual referral to confirm eligibility and check readiness to participate; if willing the individual was booked to attend an appropriate DESMOND programme. Practice nurses and DESMOND co-ordinators were instructed not to tell individuals which type of course they would be attending.

### Collection of baseline and follow-up data

Participants were sent a questionnaire booklet containing a set of questionnaire tools (Table 1) which they were asked to complete and bring to the programme. Upon attendance, prior to the programme commencing, written informed consent was taken by the educators. Participants were informed which arm of the study they were allocated to after informed consent was established and the programme started.

Biomedical data collected at diagnosis by the primary care team (see Table 1) were sent to the local DESMOND team. These constituted baseline data for participants who consented to join the study.

Follow-up data are collected by practice nurses at 6, 12 and 18 months post-programme. Two weeks before each follow-up date, the DESMOND Research Office sends participants a letter asking them to complete and return an enclosed questionnaire. The letter also asks them to contact their general practice and arrange an appointment for the study measures to be made. The practice is sent a letter at the same time, asking them to collect the information and return it to the research office. A reminder letter and questionnaire are sent to the participant after four weeks if the questionnaire has not been returned; practices who do not return follow-up data are contacted and prompted for the information. If, for some reason, data are not collected at a follow-up point, the participant is approached at the subsequent follow-up, unless they have been formally withdrawn from the trial.

### Study intervention

The study intervention is the DESMOND Newly Diagnosed structured education programme with specific sessions on SMBG, compared with the same programme with specific sessions on self-monitoring of urine glucose [32]. The standard programme involves 6 h of contact time, facilitated by two trained HCPs. The content of the curriculum is designed for people attending within 12 weeks of diagnosis and focuses on cardiovascular risk factors and associated lifestyle factors, such as food choices and physical activity. The broad content of the curriculum has been reported elsewhere [33]. The HCPs attend a formal training programme in order to be accredited as DESMOND Educators [34]. A quality development pathway and specifically developed and tested quality assurance tools are used to ensure consistency of delivery.

The standard DESMOND Newly Diagnosed programme includes a 20 min session on self-monitoring which covers the difference between short term and long term monitoring of blood glucose, without detailed coverage of the different methods, and forms a relatively small part of the programme. However, for the purpose of the trial, the session on self monitoring has been extended in length and content. The development, piloting and content of the self-monitoring sessions for the trial and the training of the DESMOND educators are described below.

### Development and piloting of self-monitoring sessions

Experienced DESMOND trainers developed and piloted the new self-monitoring sessions using an iterative cycle. Six educators from 3 PCTs were then trained in delivery of the sessions before delivering it incorporated into the DESMOND programme to patients in their area. Subsequently the educators provided feedback which led to revision of the sessions and resources.

The 6-h DESMOND structured education programme is underpinned by a philosophy and learning theories that promote adult learning through interactive step-wise processes, which increase self-efficacy to promote self-management [33]. Therefore, the newly developed monitoring sessions needed to reflect these principles.

The content of the self-monitoring sessions is summarised in Table 2. It was delivered in two separate sessions, totalling 100 min in length. They were embedded within the DESMOND education programme, which for the purpose of this study is delivered in two sessions, one to two weeks apart. Resources were developed for use within the sessions to enhance participant interaction and self confidence, support a reflective approach to self-monitoring, and identify self management changes in relation to results. The approach to self-monitoring is not directive and regimented but promotes the practice of self-monitoring as a tool to support decision making in regard to lifestyle changes and medication. Participants were encouraged to decide when and how often to monitor, how to interpret the results and to explore options for change. Although they were allocated randomly to either the blood or urine method of monitoring, they are able to swap methods or to stop monitoring if they choose. Participants were asked to report any change in method on the 6, 12 or 18 month questionnaire.

**Table 2 T2:** Contents of sessions on self-monitoring included in DESMOND programme in trial

Session 1	Monitoring and measuring blood glucose levels (20 mins)
	
	• Long term blood glucose control using HbA1c and recommended targets
	• How measurement of long term glucose control differs from self monitoring
	• Introduction to Health Profile
	
	Methods of self monitoring (20 mins) *
	
	• Purpose of self monitoring and how to use the information
	• How and when to monitor blood/urine
	• Target levels for blood/urine monitoring
	
	Purpose of self monitoring (20 mins)
	
	• Purpose of self monitoring and how each individual can use the information he/she gathers
**Session 2 (1 to 2 weeks later)**	Monitoring, feedback and action planning (40 mins)
	• How to interpret test results, identify personal targets and act on them
	• Key messages related to self-monitoring
	• Importance of confidence score
	• How to action plan for self monitoring

* Content varied depending on whether the session was covering urine or blood monitoring

### Methods of self-monitoring

The first session involves experiential learning with the method of self-monitoring allocated. Participants in the blood monitoring arm were taught how to use the Ascensia Contour meter; those in the urine monitoring arm were taught how to use Diastix urine strips and all participants were provided with two pots of test strips. In the second session they were encouraged to discuss their monitoring experiences and challenges. During the study participants obtain further supplies of strips by repeat prescription from their practice. The majority of study participants are exempt from prescription charges, but there is a procedure in place to enable those who are not exempt to reclaim the cost.

### Training of educators

To maximise fidelity of the intervention, educators were trained to deliver these expanded monitoring sessions. The training consisted of an initial training course (1 1/2 days) which included modelling of delivery of the self-monitoring sessions by the trainers. A second training course (1 day) halfway through the study provided an update and the opportunity to deliver the sessions to their peers and receive feedback.

The training included a session designed specifically to: 1) inform educators about the concept of equipoise - agreement in the scientific community that there is genuine uncertainty whether one treatment is more beneficial than another, [35] and 2) raise educators' awareness of their own views about the two monitoring methods (i.e. the two arms of the trial). This included reflection on how their personal beliefs, attitudes and behaviours might impact on their delivery of the sessions and in turn the outcome of the study. It is important to note that the training was not designed to achieve a position where every educator was considered to be in individual equipoise regarding self-monitoring. Rather, it enabled educators to explore and recognise their personal beliefs and how these beliefs may impact on their delivery of the intervention, and to learn behaviours that would prevent this type of impact.

The educators' beliefs about self-monitoring were assessed using a bidirectional linear scale [36]. The scale consisted of a 5 m ribbon placed on the floor with the ends labelled 'blood monitoring' and 'urine monitoring' and the centre labelled 'neutral'. The educators were asked to position themselves on the line in a place that reflected their views and beliefs about the two methods of monitoring. Initially the task was done individually without other educators observing; the task was then used in a group setting to create an opportunity for discussion of the concept of equipoise and the potential impact of beliefs on delivering the intervention.

During the trial, DESMOND trainers observed the educators delivering the sessions in order to ensure that delivery reflected the curriculum and was not biased with regards to the method of monitoring, and to provide feedback and support to the educators.

### Involvement of practice nurses

Practice nurses based in participating practices are involved in providing care and support for participants over the 18 months of the study. They also provide repeat prescriptions for monitoring strips. A total of 75 practices are taking part in the study and it was therefore not possible to provide extensive training to the practice nurses involved. Each nurse received a one hour visit from a member of the research team which covered the study's standard operating procedures for the collection of data and the importance of being impartial and neutral when they discussed monitoring methods with the participant. They were encouraged to follow the approach used by DESMOND educators to help the participant self-manage their diabetes.

### Analysis

#### Power calculations and sample size

The aim is to show equivalence in mean HbA1c at 18 months of within ± 0.5%. Assuming a standard deviation (SD) at 18 months of 1.5%, [37] the sample size required without allowing for clustering for 80% power at 5% significance is 142 per arm. With an intra-cluster correlation of 0.05, [38] and an expected mean cluster size of 5, adjustment for clustering brings the number required to 170 per arm. Assuming 20% drop out and 20% non-consent, the numbers required are 266 referrals and 213 consents per arm.

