**Methods/Design:**

The DESMOND SMBG trial is comparing two monitoring strategies (blood glucose monitoring and urine testing) over 18 months when incorporated into a comprehensive self-management structured education programme. It is a multi-site cluster randomised controlled trial, conducted across 8 sites (7 primary care trusts) in England, UK involving individuals with newly diagnosed Type 2 diabetes.

The trial has 80% power to demonstrate equivalence in mean HbA1c (the primary end-point) at 18 months of within ± 0.5% assuming 20% drop out and 20% non-consent. Secondary end-points include blood pressure, lipids, body weight and psychosocial measures as well as a qualitative sub-study.

Practices were randomised to one of two arms: participants attend a DESMOND programme incorporating a module on self-monitoring of either urine or blood glucose. The programme is delivered by accredited educators who received specific training about equipoise. Biomedical data are collected and psychosocial scales completed at baseline, and 6, 12, and 18 months post programme. Qualitative research with participants and educators will explore views and experiences of the trial and preferences for methods of monitoring.

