### Presentation of the hypothesis

Our null hypothesis is that use of SMBG rather than urine monitoring in the context of delivering the DESMOND intervention will not be equivalent in terms of improving and sustaining glycaemic control over 18 months.

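### The sample size comes from a formula for detecting a difference, so the claimed 80% power for equivalence within ±0.5% is about 75% (90% CI) or 60% (95% CI)

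*Protocol article*

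**What the plan says.** The trial is framed throughout as an equivalence trial. The abstract (Methods/Design) states: "The trial has 80% power to demonstrate equivalence in mean HbA1c (the primary end-point) at 18 months of within ± 0.5"%. The section Power calculations and sample size opens with the same target: "The aim is to show equivalence in mean HbA1c at 18 months of within ± 0.5"%. Presentation of the hypothesis makes non-equivalence the null, so that rejecting it demonstrates equivalence: "Our null hypothesis is that use of SMBG rather than urine monitoring in the context of delivering the DESMOND intervention will not be equivalent".

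The calculation itself is in Power calculations and sample size. The inputs are "Assuming a standard deviation (SD) at 18 months of 1.5"%, 80% power and 5% significance. The result is that "the sample size required without allowing for clustering for 80% power at 5% significance is 142 per arm". Clustering is then allowed for ("With an intra-cluster correlation of 0.05", mean cluster size 5), and "adjustment for clustering brings the number required to 170 per arm". Finally: "Assuming 20% drop out and 20% non-consent, the numbers required are 266 referrals and 213 consents per arm".

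The section names no formula. It does not say whether the 5% is one-sided or two-sided, which confidence interval decides equivalence, or what true difference is assumed.

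**The concern.** Showing equivalence within ±0.5% means excluding both +0.5% and −0.5%. Both one-sided tests must succeed, so the trial can fail on either side. A formula that allows for failure on one side only gives too small a number for the same power. The figure of 142 looks like the result of such a formula.

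If so, the main operating characteristic of the trial is overstated in two places. It also feeds a stated consequence: under Implications of the hypothesis, failing to reject non-equivalence leads to SMBG not being recommended. With two identical methods, that outcome would occur more often than the 20% that the stated power implies.

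**Working it through.** **Inputs**

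- From Power calculations and sample size: margin 0.5%, SD 1.5%, 5% significance, 80% power, ICC 0.05, mean cluster size 5, 20% drop-out and 20% non-consent.
- Assumed: equal allocation (the per-arm numbers are equal) and a true difference of 0, which is the most favourable case for equivalence.
- Not stated, so both cases are shown: a 90% CI (two one-sided tests at 5%) or a 95% CI (two one-sided tests at 2.5%).

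**1. Reproducing the plan's figures**

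Two-sided test of no difference:
n = 2 (z₀.₉₇₅ + z₀.₈₀)² (SD/δ)² = 2 (1.960 + 0.842)² (1.5/0.5)² = 141.3, rounded up to **142**.

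A one-directional non-inferiority calculation at one-sided 2.5% gives the same number. At one-sided 5%, either formula gives 112.

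The later steps reproduce:

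- design effect 1 + (5 − 1) × 0.05 = 1.20, and 142 × 1.20 = 170.4, against 170 stated;
- 170 / 0.8 = 212.5, against 213 consents;
- 213 / 0.8 = 266.25, against 266 referrals.

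The fault is therefore confined to the base number of 142.

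**2. The equivalence formula**

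At a true difference of 0, the 20% type II error is split over two sides, so z₀.₉₀ = 1.282 replaces z₀.₈₀ = 0.842. Results use unrounded quantiles.

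- 90% CI: 2 (1.645 + 1.282)² × 9 = 154.1, so **155 per arm**, 9% above 142.
- 95% CI: 2 (1.960 + 1.282)² × 9 = 189.1, so **190 per arm**, 34% above 142.

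Neither version gives 142.

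**3. Power at the planned size**

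The 170 analysed per arm, divided by 1.20, is worth about 142 per arm. The standard error is 1.5 × √(2/142) = 0.178. At a true difference of 0:

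Power = 2Φ(0.5/SE − z) − 1, with 0.5/SE = 2.81.

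| True difference | 90% CI (z = 1.645) | 95% CI (z = 1.960) |
|---|---|---|
| 0 | 75.6% | 60.4% |
| 0.1% | 68% | 53% |
| 0.2% | 51% | 37% |

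For a non-zero difference d, power = Φ((0.5 − d)/SE − z) + Φ((0.5 + d)/SE − z) − 1. A simulation using the t distribution at zero difference gives 75.3% and 60.0%.

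**4. What would restore 80%**

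By a larger trial:

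| Deciding interval | Unclustered | × 1.20 | Consents (/0.8) | Referrals (/0.64) |
|---|---|---|---|---|
| 90% CI | 155 | 186 | 233 | 291 |
| 95% CI | 190 | 228 | 285 | 357 |

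By baseline adjustment: a baseline to 18-month correlation r multiplies the residual variance by 1 − r². The planned size supplies 142 / (2 × 9) = 7.889, where equivalence needs 8.564 (90% CI) or 10.507 (95% CI). Hence r = √(1 − 7.889/8.564) = **0.28**, or r = √(1 − 7.889/10.507) = **0.50**. This assumes that adjustment leaves the ICC unchanged.

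**5. Unequal cluster sizes (secondary)**

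The factor 1.20 treats all practices as equal in size. The article gives no spread. If the coefficient of variation (CV) of cluster size is assumed to be 0.4 to 0.8, the design effect 1 + ((1 + CV²) × 5 − 1) × 0.05 is 1.24 to 1.36. Power at zero difference is then 74% to 68% (90% CI) or 58% to 50% (95% CI). Efficient weighting in the GEE would soften this somewhat. The main conclusion does not depend on it.

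**The case against.** The strongest reply is that the size of the error depends on something the article does not state. Two one-sided tests at 5% is a common reading for equivalence. On that reading the shortfall is only 4 to 5 points; the 20-point shortfall needs a 95% interval. The only 95% interval mentioned in the analysis sections is in Economic evaluation, and it does not settle the rule for HbA1c. This stands, and it is why both figures are given. However, 142 itself requires z = 1.960, since a one-sided 5% value gives 112. The plan's own arithmetic therefore sits closer to the 95% case.

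A second reply is that the analysis described will do better than the calculation. Statistical analysis plans adjustment for baseline and an average of continuous outcomes over time. As an illustration, assume three follow-up visits with equal SDs and between-visit correlations of 0.4 to 0.7. Averaging would then give power of about 87% to 95% (90% CI) or 76% to 90% (95% CI) at zero difference. But an average over follow-up is not the 18-month endpoint for which power is claimed, so it cannot support that claim. Baseline adjustment could support it, but the calculation takes no credit for it and cites no correlation. Baseline here is HbA1c at diagnosis, before education and 18 months of care, so 0.50 cannot be taken for granted.

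It is also true that the error does not invalidate the final confidence interval or inflate the type I error; it raises the chance of an inconclusive result. The recommendation attached to such a result is a separate matter, though it adds to the consequence.

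Finally, this is not detail left to an analysis plan. The article prints a sample size and a power, and they do not match.

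**Conclusion.** The concern holds. The figure of 142 per arm answers a different question from the one the trial asks. For the unadjusted 18-month comparison with SD 1.5%, ICC 0.05, equal clusters of 5 and a true difference of exactly 0, the power to show equivalence within ±0.5% is about 75% (90% CI) or 60% (95% CI), not 80%. The chance of failing to show equivalence between identical methods is about 25% or 40%, against the 20% implied. Under the stated SD and without covariate adjustment these are best-case figures, because any true difference lowers them. Baseline adjustment may make up the shortfall, but nothing in the article establishes that it does.

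**What to change.** In Power calculations and sample size:

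- State which interval decides equivalence, 90% or 95%, and fix this before the analysis.
- Restate the power for 170 analysed per arm as about 75% (90% CI) or 60% (95% CI), for the unadjusted 18-month difference at a true difference of 0.
- If credit is taken for baseline adjustment, say so and cite a supported baseline to 18-month correlation. About 0.28 (90% CI) or 0.50 (95% CI) is needed for 80%.

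Correct the power statement in the abstract to match.

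Restating the power needs no change to recruitment. Keeping the 80% claim at the present size is justified only if such a correlation can be supported. The cost is wording in two places and a less favourable stated power.
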